## Abstract

**Background:**

Advance care planning (ACP) involves proactive communication about end-of-life care preferences among patients, families, and health care providers. In Chinese culture, older adults commonly delegate such care decisions to adult children, yet family reluctance—rooted in beliefs that aggressive treatments are beneficial—remains a major barrier to ACP participation. Existing interventions improve documentation and communication through education, hypothetical scenarios, and physician engagement, but few target family members specifically or use a theoretical framework. The transtheoretical model is particularly underused for assessing family readiness. Infographics, videos, and large language models demonstrate strong potential for engagement, highlighting the need for tailored, theory-driven family empowerment interventions.

**Objective:**

This study aims to evaluate the feasibility, acceptability, and preliminary efficacy of a 10-day digital intervention (ChatACP) designed to empower family members to support care home residents in ACP.

**Methods:**

An explanatory sequential mixed methods study using a pilot randomized controlled trial with a postintervention and 3-month assessment and a posttrial qualitative study will be conducted. Eligible family members (N=60) of care home residents from 6 homes will be enrolled. The intervention group will receive ChatACP, and the control group will receive a self-learning ACP pamphlet. The ChatACP intervention consists of 2 phases. Phase 1 includes a 10-day series of ACP educational infographics, video clips, and a content-specific chatbot on ACP knowledge in Hong Kong. Upon completion of phase 1, those not advancing to the action stage will receive phase 2 of a nurse-led telephone consultation.

**Results:**

This project was recommended for support in September 2025. Recruitment and data collection will commence in September 2026. Primary outcomes of feasibility and acceptability include rates of recruitment, retention, fidelity, engagement, usability, and safety. Secondary outcomes include the family members’ ACP readiness, engagement, and completion of ACP activities. The feasibility and acceptability outcomes will be compared to predefined progress criteria. Preliminary efficacy outcomes will be analyzed using a generalized mixed-effects model.

**Conclusions:**

The study will inform whether the ChatACP intervention can empower families on ACP. Findings from this study can inform the development of large-scale interventions to improve ACP engagement among family members of care home residents.

**Trial Registration:**

ClinicalTrials.gov NCT07448649; https://clinicaltrials.gov/study/NCT07448649

**International Registered Report Identifier (IRRID):**

PRR1-10.2196/94883

## Introduction

Advance care planning (ACP) is “an overarching process of proactive communication regarding end-of-life care” among patients, family caregivers, and health care providers [1]. Unlike Western conventions, Chinese parents often rely on their children for emotional and financial security and care decision-making in their later years, assuming that it is a natural outcome of the sacrifices and resources they invested in raising their children [2]. However, one randomized controlled trial (RCT) found family objections a key barrier to older individuals’ participation in ACP activities [3]. Given family members’ reluctance to discuss their loved ones’ end-of-life (EOL) care preferences, stemming from the belief that aggressive therapies are the most beneficial, interventions are necessary to empower them to alter their perspective.

A meta-synthesis of 17 qualitative studies [4] on family members’ experiences with ACP in nursing homes revealed that family members lacked knowledge and awareness of the timing and goals of ACP. In addition, there were 28 studies, including 14 RCTs and 14 nonrandomized experimental studies retrieved from both Chinese- and English-language databases [5,6], that demonstrated effectiveness in completing advance medical directive documentation (odds ratio [OR] 7.58, 95% CI 1.41-40.63; *P*=.02) and proactive communication with physicians (OR 2.42, 95% CI 1.42-4.12; *P*=.001). A total of 20 studies [5,6] adopted ACP education interventions (information manual, videos, goal-of-care statement, and interactive websites) in promoting ACP awareness. Trained nurses, social workers, physicians, or trained laypeople delivered 11 to 120 minutes of ACP consultations. Additional components focused on engagement with care providers. Four previous studies examined the use of hypothetical stories to have participants reflect from a third-person point of view [7-10]. Group visits, mindfulness activities, and card games have introduced EOL topics in a supportive atmosphere [11-13]. One study investigated a coaching session on asking care providers about EOL care preferences [14]. Thus, for an ACP empowerment intervention, ACP education and care provider engagement are 2 key components.

None of the existing interventions have reported detailed information on how to empower family members or are guided by a conceptual framework. While the transtheoretical model (TTM) has been widely used to understand the stages of change (precontemplation, contemplation, preparation, action, and maintenance stages) for ACP among older adults [15], its potential for informing and enhancing social and behavioral interventions for family members remains underused [16]. The Hong Kong Hospital Authority recommended that ACP should be sensitive to assessing the readiness of the patient and family members to continue the conversations and a rigid or routinized approach should be avoided [1]. Therefore, there is a pressing need for research that investigates the application of the TTM in designing targeted ACP empowerment interventions for family members.

Compelling evidence supports infographics and videos for patient education as they also lower patient anxiety [17,18]. Large language models (LLMs) such as the generative pretrained transformer series and DeepSeek have demonstrated capabilities in answering queries when trained using targeted content in a user-friendly language, and they show significant promise for enhancing patient engagement [19,20]. To empower family members to participate in their loved ones’ ACP, our team has developed the evidence-based, theory-driven ChatACP intervention. ChatACP leverages the strengths of infographics and video instruction, tailoring them to family members in the precontemplation and contemplation stages while also providing interaction with an LLM-based chatbot specializing in ACP and consultation with a research nurse for those in the preparation stage.

## Methods

### Aims

The study aims to evaluate (1) the feasibility and acceptability of ChatACP and (2) the preliminary efficacy of ChatACP on family members’ readiness for ACP, engagement in ACP, and completion of ACP activities, in comparison to those who received a self-learning handout, at the postintervention time point and 3-month follow-up.

### Design

This will be an explanatory sequential mixed methods study including a pilot cluster RCT followed by a posttrial qualitative study with a postintervention time point and 3-month follow-up, as shown in the trial flowchart (Figure 1), over 2 years. To prevent contamination, we will enroll 6 care homes (N=60 family members of residents) and randomly assign 3 homes to receive ChatACP and 3 to receive the ACP self-learning handout.

**Figure 1 figure1:**
[figure not shown]
Trial flowchart. ACP: advance care planning; T0: baseline; T1: postintervention time point; T2: 3-month follow-up.

### Inclusion Criteria

The inclusion criteria are as follows: (1) age of 18 years or above; (2) providing care for an older adult (aged 65 years or older) living in a care home as a primary family caregiver (including family members in the traditional sense and the guardians and persons close to or significant to the older adult); (3) ability to read, write, and communicate in Cantonese or Mandarin; (4) the resident (care recipient) having a prefrail or frail status as defined by a score of 2 or above on the FRAIL scale [21]; (5) having a mobile device to receive instant messages and access to a cellular network; and (6) having engaged in minimal or no prior EOL care discussions with the care home resident as defined by a self-reported status of being in the precontemplation or contemplation stage regarding ACP discussions with the resident using the ACP staging algorithm illustrated in Figure 2 [22].

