### Exclusion Criteria

The exclusion criteria are as follows: (1) moderate to severe cognitive impairment, defined by an Abbreviated Mental Test score [23] of 5 or less, and inability to give consent; and (2) communication problems (eg, deafness or aphasia).

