#### Completion of ACP Activities

Participants will report a binary response of “yes” or “no” on six behaviors widely used to evaluate ACP outcomes [15]: (1) complete the designation of a health care proxy for the resident; (2) communicate with the resident about their views on life-sustaining treatment and (3) quality vs quantity of life; (4) help residents’ communicate with their health care providers regarding resident’s views on the use of life-sustaining treatment and (5) quality vs quantity of life; and (6) help the resident complete their EOL care paperwork, such as documenting ACP in health medical records and advance medical directives or do-not-attempt-cardiopulmonary-resuscitation forms.

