### Data Collection

The preliminary efficacy outcomes will be collected among participants in both arms at baseline (T0; before the intervention), after the intervention (T1), and at 3 months (T2). The feasibility of the proposed study will be evaluated using the feasibility and acceptability outcomes at the end of data collection. Following the completion of the T2 survey, participants will receive HKD 200 (HKD 1=US $0.13 as of June 5, 2026) supermarket coupon as an incentive.

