### Analysis

Data will be analyzed in SPSS software (IBM Corp). Data will be screened for completeness, and the RA will contact participants if there are any missing data. Descriptive statistics will be used to summarize participant characteristics and study outcomes.

The preliminary effect outcomes (family members’ ACP readiness, engagement, and completion of ACP activities) will be analyzed using a generalized linear mixed-effects model to understand the treatment differences at each time point. Because data are nested within each care home (cluster), observations within the same cluster may be correlated, violating the assumption of independence. To account for this clustering effect, we will integrate a random intercept for care homes in the generalized linear mixed-effects model. Given that our study is not powered to examine effectiveness, the outcomes will be reported with the standardized effect size (scores for ACP readiness and engagement) or ORs (completion of ACP activities) with a 95% CI. A Cohen *d* of 0.2, 0.5, and 0.8 and an OR of 1.5, 2.5, and 4 will indicate small, medium, and large effect sizes, respectively.

The feasibility and acceptability outcomes will be assessed to determine the progression to a full multisite RCT based on the predefined progression cutoffs outlined in the outcome measurements section, which include a 50% recruitment rate, 70% retention rate, 90% intervention fidelity, 50% intervention engagement rate, 78% content usability, 70% acceptability, and 100% safety based on prior review [30].

For the qualitative evaluation, the voice-recorded interviews will be transcribed verbatim and then analyzed according to the thematic analysis proposed by Braun and Clarke [31]. The NVivo software (Lumivero) will be used to manage the collected qualitative data and support the analysis. To ensure rigor, credibility, transferability, dependability, and confirmability will be assessed. Findings from both the qualitative and quantitative portions after completing the qualitative study will be synthesized. A sequential interpretive integration of both types of data will be undertaken at the interpretation stage.

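### Completion items 1 and 6 have no since-baseline window and no stated use of the T0 answer, so a proxy or paperwork completed before enrolment may enter the T1 and T2 odds ratios

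*Protocol article*

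**What the plan says.** **Eligibility.** In the protocol article, Inclusion Criteria, item 6 asks for relatives "having engaged in minimal or no prior EOL care discussions with the care home resident as defined by a self-reported status". The defining status is a "self-reported status of being in the precontemplation or contemplation stage regarding ACP discussions with the resident". The Exclusion Criteria cover cognition with inability to consent, and communication problems. Neither list mentions an existing proxy, ACP record, advance medical directive or DNACPR form.

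**Outcome.** Completion of ACP Activities lists six behaviours that the relative reports as yes or no. Item 1 is "complete the designation of a health care proxy for the resident". Item 6 is "help the resident complete their EOL care paperwork, such as documenting ACP in health medical records and advance medical directives or do-not-attempt-cardiopulmonary-resuscitation forms". No recall window is given. Under Preliminary Efficacy Outcomes and again under Data Collection, these measures are taken in both arms at T0, T1 and T2.

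**Analysis.** The Analysis section specifies a "generalized linear mixed-effects model to understand the treatment differences at each time point", with a random intercept for care home. Completion is reported as ORs with 95% CIs, and "an OR of 1.5, 2.5, and 4 will indicate small, medium, and large effect sizes". No baseline adjustment or restriction to new completions is stated.

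**The concern.** The screen and the outcome cover different things. A relative can truthfully be in precontemplation or contemplation about talking with the resident while a proxy was settled or a form completed earlier. The stage criterion largely covers items 2 and 3, which concern talking with the resident, but it does not reach items 1 and 6. Provider communication (items 4 and 5) is not screened directly either, but the gap is clearest for the two items that can be finished once and then stay finished.

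Two consequences follow if such relatives answer yes at follow-up:

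- With a similar share in both arms, the same block of yes answers is added to each side, and the OR moves towards 1.
- With unequal shares, part of the between-arm difference is prior documentation rather than intervention effect. Homes are pair matched only on public or private type, with three per arm. A random intercept for home allows for correlation within homes, but it does not remove a difference between arms in what was already in place.

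Completion is part of the second aim, its OR is to be labelled small, medium or large, and the Discussion looks ahead to a larger trial assessing ACP documentation. A distorted label could be carried into that trial's planning.

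**Working it through.** The plan states no completion rate, prior-completion share or power figure, so there is no figure to reproduce. The calculation shows how far the OR could move.

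**Inputs**

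- From the article: OR bands 1.5 / 2.5 / 4; 60 relatives in 6 homes, 3 per arm, so about 60/2 = 30 per arm.
- Assumed: new completion among those with nothing in place is 10% (control) and 25% (intervention); a share q had completed the item before enrolment and answers yes throughout. One item is considered at a time.

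**Formulas.** Observed rate = q + (1 − q) × p. OR = [p₁/(1 − p₁)] / [p₀/(1 − p₀)].

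**Equal q in both arms**

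| q | Intervention | Control | Observed OR | Band |
|---|---|---|---|---|
| 0 | 0.250 | 0.100 | (0.25/0.75)/(0.10/0.90) = 3.00 | medium |
| 10% | 0.1 + 0.9 × 0.25 = 0.325 | 0.1 + 0.9 × 0.10 = 0.190 | 2.05 | small |
| 30% | 0.3 + 0.7 × 0.25 = 0.475 | 0.3 + 0.7 × 0.10 = 0.370 | 1.54 | small |
| 50% | 0.5 + 0.5 × 0.25 = 0.625 | 0.5 + 0.5 × 0.10 = 0.550 | 1.36 | below small |

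The extent depends on the control rate. A true OR of 4 seen at q = 10% becomes 2.03, 2.58 or 3.14 for control new-completion rates of 5%, 10% or 20%.

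**Unequal q, no intervention effect (10% new completion in both arms)**

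- q = 40% intervention v 20% control: 0.46 v 0.28, OR = (0.46/0.54)/(0.28/0.72) = 2.19.
- q = 30% v 10%: 0.37 v 0.19, OR = 2.50. The reverse imbalance gives 0.40.

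**The other reading of the items.** Suppose relatives whose resident already has a form answer no, because they did not arrange it themselves, and cannot complete it again. Then the observed rate = (1 − q) × p. At q = 30%: 0.175 v 0.070, OR = (0.175/0.825)/(0.070/0.930) = 2.82. The OR hardly moves, so the size of the problem depends on how the items are understood.

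**Restriction to T0 = no.** Those reporting prior completion leave numerator and denominator: (1 − q)p/(1 − q) = p. The first table returns to OR 3.0 at every q, and the null examples return to 1.0. At q = 30%, about 30 × 0.7 = 21 per arm remain for that item; at q = 10%, 27.

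**The case against.** A reader might infer that any resident with an existing proxy, directive or DNACPR form is automatically counted as completed. The documents do not say so. Participants report their own behaviours, and item 6 is worded as the relative helping, so a form raised by others could properly be answered no. Item 1 can be read in the same way. The scoring is ambiguous; it is not fixed at yes.

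A reader might also conclude that such families should be excluded. The criterion aims at relatives who have hardly discussed end-of-life care, and a relative who avoids that discussion although a form exists is still someone the intervention is meant to reach. Excluding them would narrow the target population and shrink the pool of a feasibility pilot.

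Further points stand. The items are collected at T0, so prior completion, as reported, is identifiable and an imbalance could be seen. The limitations already concede vulnerability to baseline imbalance. The interval will be wide: at 30 per arm, ignoring clustering, 25% v 10% gives SE(log OR) = √(1/7.5 + 1/22.5 + 1/3 + 1/27) = 0.74 and a 95% CI of about 0.7 to 13, so the dilution lies well inside it. Handling of T0 answers could also be settled in an analysis plan that is not shown.

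These points limit the concern without removing it. Seeing T0 balance does not undo dilution, which occurs when the arms are perfectly balanced. The article does state its contrast, and that contrast makes no stated use of T0. The recall window is part of the question put to participants, so it has to be right before data collection; an analysis plan cannot reword it afterwards.

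**Conclusion.** The point holds in a limited form. Eligibility screens discussion stage only, items 1 and 6 have no since-baseline window, and the stated comparison does not use the T0 answer. Following the plan as written, completions that predate the trial may enter the T1 and T2 ORs. On the assumed rates, an OR of 3.0 would be reported as about 2.05 at 10% prior completion and 1.54 at 30%, which moves it from medium to small on the plan's own bands. An imbalance of 40% v 20% with no effect would give about 2.2.

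These sizes rest on assumed rates, on an unknown share q, on relatives answering yes for earlier completion, and on T0 not being used. They concern two of six items. It does not follow that the outcome as a whole is invalid or that the eligibility criterion is wrong. Severity is minor to moderate: completion is secondary, the study is declared not powered for effectiveness, and progression rests on recruitment, retention, fidelity, engagement, usability, acceptability and safety.

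**What to change.** Leave inclusion criterion 6 unchanged. Then:

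1. Word items 1 and 6 at T1 and T2 as completion since baseline, and make clear whether the relative's own action is required. At T0, ask whether the item has already been completed.
2. Analyse items 1 and 6 at T1 and T2 among participants answering no to that item at T0, or adjust for the T0 answer. Restriction is the simpler choice: if everyone with a T0 yes stays at yes, a logistic model adjusting for T0 will have a separated covariate.
3. Report T0 completion of each item by arm and by home.

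The cost is a few words in the questionnaire and one or two sentences in the analysis text; the T0 visit and its items are already planned. The downside is that fewer participants contribute to these two items, with wider intervals. Relatives who answer no at T0 although others have already completed the form would remain in the denominator, but on the figures above this leaves only slight dilution (2.82 against 3.0 at a 30% share). Recruitment is due to start in September 2026, so the wording is easiest to change before then.

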**Figure 2 figure2:**
[figure not shown]
Theoretical framework for the ChatACP intervention based on the advance care planning (ACP) staging algorithm (adapted from Fried et al [22]).

### Exclusion Criteria

The exclusion criteria are as follows: (1) moderate to severe cognitive impairment, defined by an Abbreviated Mental Test score [23] of 5 or less, and inability to give consent; and (2) communication problems (eg, deafness or aphasia).

### Randomization

The care home will be the unit of randomization, and 6 homes will be pair matched based on type of home (public or private). An independent statistician will randomly assign one home from each pair to the intervention arm using a computer-generated algorithm.

### Treatment

#### Overview

Prior to treatment allocation, all participants will be in the precontemplation or contemplation stage. Family caregivers in the clusters of the intervention group will receive the ChatACP intervention. Family caregivers in the clusters of the control group will receive a self-learning ACP handout published by the Hong Kong Hospital Authority [24].

#### ChatACP Group

##### Overview

ChatACP encompasses a digital education component and a care provider engagement component. The digital education component (messages with ACP infographics and video clips and a chatbot with specific content for ACP for 10 days) was developed to help family members in the precontemplation or contemplation stage in progressing to the preparation stage by enhancing their understanding of the value of ACP discussions. The care provider engagement component (nurse-led telephone consultation) was designed to coach family members in the preparation stage to advance to the action stage by formulating an action plan for initiating ACP with their loved ones.

##### Phase 1 (Digital Education)

Participants will receive the ChatACP education component (ACP infographics and video clips and access to a 24/7 ACP chatbot for 10 days) delivered via their preferred messaging platform (eg, WhatsApp, WeChat, or Line) by the research nurse. Participants will also be advised to submit their ACP queries through the chatbot or by messaging the research nurse. The nurse will respond to queries during working hours. Participants will be encouraged to share the content with the resident and other family members. To safeguard participant privacy, each participant will be assigned a unique study ID for identification, and participants will be instructed to avoid disclosing any personally identifiable information on the messaging platform or chatbot. All the chatbot and message logs will be collected and securely saved in a cloud drive at the University of Hong Kong. Access to the data is restricted solely to the research team, and no external platforms are permitted access.

ACP infographics (Table 1) were developed for care home settings by incorporating ACP teaching materials from Singapore, the United Kingdom, the United States, and Canada. The main content consists of educational materials on EOL care, hypothetical scenarios, and communication skills. A panel of local health professional experts and laypersons appraised the ACP content and provided feedback as well. We tailored the ACP infographics according to the TTM of readiness to change, adjusting the content from simple to advanced. These infographics were segmented into a 10-day delivery format.

ACP video clips were also developed based on the 10-day infographic protocol. A total of 10 videos of 1 to 2 minutes with infographics, animated illustrations, subtitles, and audio were made by our team using artificial intelligence–powered visual communication tools.

The ACP chatbot was developed on the cutting-edge open-source LLM DeepSeek-R1 [25], which ensured the baseline conversational intelligence, and then customized to have ACP expertise by feeding it specific knowledge compiled by our team. The database includes local ACP guidelines and a document including frequently asked questions and answers gathered from older adults, family caregivers, and care providers from care homes. The ACP chatbot was also designed to draft responses at a fifth-grade reading level. The ACP chatbot functions as a search engine specialized in ACP; family members can access the chatbot via a web link 24/7. The accuracy of the chatbot will be evaluated internally prior to deployment for participant use. The chatbot has been prompted to not provide clinical advice and to direct participants expressing distress to contact the research nurse for immediate support during working hours (9 AM to 6 PM, Monday to Friday). The research nurse is an experienced Respecting Choices–certified ACP facilitator who has successfully managed over 100 cases of ACP for older adults and their families in Hong Kong. All the conversations within the chatbot will be reviewed by the research assistants (RAs) for accuracy and appropriateness daily during the intervention period. In the event of detecting inaccurate or improper responses from the chatbot, RAs will escalate the case to the research nurse to directly approach the participants via the messaging platform to provide clarification on the chat content.

**Table 1 table1:** ChatACP educational infographic messaging protocol.

Day	Topic of the infographics
1	What is advance care planning? Disease trajectories at the end of life Hypothetical scenarios and guidance for common family member issues
2	Why plan ahead? Hypothetical scenarios and guidance for common family member issues
3	First step: understanding the patient’s needs and wishes
4	Second step: the timing of communication with family members
5	Third step: communicating with the physician
6	The role of the family member as a spokesperson for medical decision-making
7	Life-prolonging treatments, including cardiopulmonary resuscitation, assisted ventilation, artificial nutrition and liquid feeding, blood transfusions, and dialysis
8	What is an AMD^a^? Points to note when signing an AMD Hypothetical scenarios and common issues faced by family members
9	How can family members initiate conversations about end-of-life care with the patient? Comfort-oriented treatment Hypothetical scenarios and guidance on common issues faced by family members
10	What can family members do for patients who are terminally ill?

^a^AMD: advance medical directive.

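### In the ChatACP arm the chatbot runs round the clock, but the stated distress referral leads only to a nurse on weekday office hours, and the daily log review is not told to escalate distress

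*Protocol article*

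**What the plan says.** All of the relevant text is in the Protocol article, Methods, mainly under Phase 1 (Digital Education).

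- **Availability.** Intervention participants get "access to a 24/7 ACP chatbot for 10 days"; the chatbot description repeats that "family members can access the chatbot via a web link 24/7".
- **Distress rule.** The chatbot has been prompted to "direct participants expressing distress to contact the research nurse for immediate support during working hours (9 AM to 6 PM, Monday to Friday").
- **Messaging the nurse.** Participants may also send queries to her on the messaging platform. "The nurse will respond to queries during working hours".
- **Log review.** "All the conversations within the chatbot will be reviewed by the research assistants (RAs) for accuracy and appropriateness daily during the intervention period".
- **Escalation.** "In the event of detecting inaccurate or improper responses from the chatbot, RAs will escalate the case to the research nurse", whose task is then "to directly approach the participants via the messaging platform to provide clarification on the chat content".
- **Later nurse contact.** Under Interim ACP Staging Assessment and Phase 2, participants who have not reached the action stage after the digital phase receive a nurse-led telephone consultation on ACP.
- **Safety outcome.** Under Intervention Safety, risk is assessed from adverse events that participants report themselves.

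**The concern.** The sponsor foresaw that some users would become distressed and wrote a rule for it. That rule ties immediate help to one person, who is off duty for most of the time that the chatbot is open. The daily review could act as a safety net, but its stated trigger and remedy both concern what the chatbot said, not how the participant is.

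The material is sensitive. Table 1 covers life-prolonging treatments on day 7, and the day 10 topic is "What can family members do for patients who are terminally ill". By the inclusion criteria, participants have had little or no end-of-life discussion with the resident. Family carers may well read this material in the evening or at a weekend, when the named contact is away. What is at stake is participant welfare in the ChatACP arm; no analysis or estimate is affected. The safety outcome does not fill the gap, because self-reported adverse events measure what happened and are not a route to help.

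**Working it through.** The plan states no figure to reproduce. The check has two parts: hours of cover, and a walk through the stated rules.

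**Inputs** (Phase 1 (Digital Education)): chatbot open 24 h a day, 7 days a week, for 10 days; nurse on duty 09:00 to 18:00, Monday to Friday. Assumptions: the 10 days are consecutive calendar days, and public holidays are ignored.

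**Cover per week**
- Nurse: 9 h × 5 = 45 h. Chatbot: 24 h × 7 = 168 h.
- Covered: 45/168 = 26.8%. Uncovered: 123/168 = 73.2%.

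**Cover over the 10 days** (24 × 10 = 240 h)

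| Start day | Weekdays in window | Nurse hours | Share of 240 h |
|---|---|---|---|
| Mon, Tue or Wed | 8 | 72 | 30.0% |
| Thu or Sun | 7 | 63 | 26.25% |
| Fri or Sat | 6 | 54 | 22.5% |

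**Wait until the nurse is next on duty**
- Monday to Thursday, 20:00: 4 + 9 = 13 h
- Friday, 20:00: 4 + 48 + 9 = 61 h
- Saturday, 12:00: 12 + 24 + 9 = 45 h
- Sunday, 12:00: 12 + 9 = 21 h
- Longest, Friday 18:00 to Monday 09:00: 6 + 48 + 9 = 63 h
- A full weeknight gap, 18:00 to 09:00: 6 + 9 = 15 h

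Whatever the start day, 10 consecutive calendar days contain exactly one complete Friday-to-Monday run. Each ChatACP participant therefore has one 63 h gap during access.

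**The rules applied to one case**
1. A user expresses distress at 20:00 on a Friday.
2. The chatbot follows its prompt and refers the user to the nurse, who is next on duty 61 h later.
3. A research assistant reads the conversation in the daily review. The reply was neither inaccurate nor improper, so the stated trigger is not met.
4. If the user leaves a message, the nurse answers it when back on duty. If not, no stated step prompts her to contact the user about the distress.

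**The case against.** The strongest objection is that this is a condensed article. Out-of-hours contacts and distress procedures usually sit in the full protocol or the ethics file, and the study has ethics approval. A step that is not stated may still exist. That stands as a limit: nobody can infer from this article that the trial has no distress procedure. It does not remove the point, because the article does not leave distress handling out. It states the referral route, the hours, the scope of the review, the trigger and the purpose of nurse contact, and the stated rule can be judged as written.

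Other objections narrow the point:

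- **Messages can wait for the nurse.** One message on Friday evening is enough to get an answer in working hours. A reader might infer that a distressed user is left with no route at all; the text does not support that.
- **The phase 2 call is human contact that the user need not start.** True, but it comes after the digital phase, goes only to those not in the action stage, and is about ACP rather than distress.
- **The prompt may already tell users the nurse's hours.** The chatbot's exact wording is not shown, so it cannot be said that users are unaware she is off duty.
- **A reply that mishandles distress could be escalated as improper.** It could. What remains is distress that the chatbot handles correctly, out of hours.
- **The tool is not a crisis service.** It is described as a specialised search engine and is told not to give clinical advice. That argues against demanding a nurse at all hours, which is not proposed here.

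A reader might also take the 24/7 access and the weekday referral as a contradiction. They are not one: the hours are stated openly. Nor does the gap reach all 60 participants, since control participants receive a handout and have no chatbot.

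**Conclusion.** The point holds for the ChatACP arm. As written, the distress rule refers an out-of-hours user to a nurse who is not on duty, and the daily review has no stated trigger for distress that the chatbot answered correctly. Neither the message channel nor the phase 2 call provides out-of-hours support or proactive follow-up of distress.

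Nurse cover is 26.8% of chatbot hours in a week and 22.5% to 30.0% over the 10 days. The 63 h maximum should not be read as a measure of harm: the article gives no rate of distress, so the risk cannot be quantified. The conclusion rests on the article as the only source, and a fuller procedure elsewhere could resolve it. This is a safety procedure worth tightening before recruitment, not a flaw that undermines the trial.

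**What to change.** First check whether the full protocol already holds an out-of-hours distress procedure; if so, state it briefly in the article. If not, make two changes under Phase 1 (Digital Education):

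1. **Chatbot prompt.** Outside nurse hours, the reply to a distressed user should say that the nurse is unavailable, give the time she can next be reached, and name an existing out-of-hours or emergency service.
2. **Daily review.** Add participant distress as an escalation trigger for the research assistants, whether or not the chatbot's reply was correct, so that the nurse contacts the participant when next on duty.

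The two changes do different work. Only the first offers help during the 63 h gap. The second does not shorten that gap, but follow-up no longer depends on the user writing to the nurse.

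The cost is small: one prompt change and one added trigger in a review that already runs, with no extra staff and no change to design, sample size or analysis. The downsides are a possible ethics amendment and the need to agree the referral service before recruitment opens in September 2026.
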